## Results

The study was funded by the National Institute of Mental Health in April 2022. Progress has been made on various aims to date. Qualitative interviews have been completed with 26 individuals, including 9 formerly incarcerated individuals, 9 county jail staff, and 9 employees of community organizations (1 individual was both a formerly incarcerated individual and an employee of a community organization). A focus group with 10 additional individuals has also been conducted. All interviews have been transcribed, coded, and analyzed, and a manuscript highlighting the key themes is in progress.

In addition, summaries of field notes for each interview have been organized into key barriers; facilitators; suggested approaches to overcome barriers; resources needed to overcome barriers; and specific strategies to improve risk assessment, HIV testing, sexual health or PrEP education during incarceration, and postrelease linkage to PrEP. Findings from these interviews have been applied to formulate a jail PrEP implementation protocol using rapid qualitative analysis.

An HIV risk prediction model based on jail EHR data to identify individuals most likely to benefit from PrEP has been developed using records from 33,458 individuals who have undergone HIV testing in jail. This model has been optimized using machine learning, has been internally validated, and is ready to be deployed. Future exercises will include integration with health system EHR data from Parkland Hospital and comparisons to parsimonious models, which will guide the iterative development of the model. We anticipate that preliminary study findings on the implementation and effectiveness of the jail PrEP implementation strategy will be available in 2026. 

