## Methods

### Study Setting

The DCJ is the main jail facility for Dallas County, with 51,000 incarcerated individuals per year (86% men, 48% Black, and 30% Hispanic) and approximately 275 individuals entering and leaving the jail daily. The mean length of stay is 45 days, and 11% of people transfer to prison [65]. Parkland Health, a teaching hospital for UT Southwestern Medical Center, provides health care services at the jail for approximately 6200 patients monthly. Health care for individuals experiencing incarceration is paid for by Dallas County.

Of over 12,000 HIV/STI tests performed each year at the DCJ, there are approximately 50 to 100 new HIV diagnoses (personal communication by [name], April 2024) and high STI positivity (5% syphilis, 5% gonorrhea, and 11% chlamydia) [35,66], which is a recommended indication for PrEP use. The approach to HIV testing at the DCJ is a combination of opt-in and opt-out. All persons entering the jail complete a nursing intake questionnaire to review medical history, receive the option for HIV/STI testing (opt-in), and, for men, indicate if they want to be in separate housing for MSM as a safety precaution. All individuals who undergo blood draws are offered opt-out HIV testing. Individuals with negative HIV test results are not routinely counseled about the results, and few, if any, receive information about PrEP. Currently, new initiation of PrEP is not permitted at the DCJ, and thus, the study will focus on linkage to PrEP after release.

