##### Validation of the HIV Risk Prediction Model

We will use our prior models for predicting incident HIV [73,74] to identify candidate variables for our HIV prediction model. Subsequently, the use of temporal validation will assess how well our model will perform prospectively, dividing our dataset into a derivation dataset (2015-2021) and a validation dataset (2022-present). We will train our model to predict incident HIV diagnoses, defined as positive HIV screening and confirmatory tests or new HIV diagnosis codes without prior evidence of HIV in the EHR [73-75]. We will have ample data on new HIV diagnoses to train our models, as Parkland has a robust HIV testing program and diagnoses more new cases of HIV than any other entity in Dallas [76]. Jail EHR data may be more limited in scope because the jail generally provides short-term episodic care. However, given high recidivism rates [77], many incarcerated individuals will have multiple data points in the jail EHR to inform HIV risk prediction, including data on prior HIV/STI testing and substance use.

We will compare the performance of parsimonious versus full models in the validation dataset based on their ability to discriminate between patients with and those without incident HIV using the C-statistic or area under the receiver operator characteristic curve and the Hosmer-Lemeshow goodness of fit test. Additionally, we will use multiple complementary approaches for estimating HIV risk to capture the greatest number of individuals with indications for PrEP. This will include anyone who identifies as transgender, requests MSM housing, has had a recent STI, or opts-in for HIV/STI testing, in addition to those flagged by our EHR model. We will compare EHR models against these criteria to measure the added value of each approach (eg, number of individuals identified by our model as likely to benefit from PrEP who are missed by patient-reported data and vice versa).

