**Figure 2 figure2:**
[figure not shown]
Intervention steps in the jail-to-community continuum. DCJ: Dallas County Jail; EHR: electronic health record; PrEP: pre-exposure prophylaxis; STI: sexually transmitted infection.

In the “identify” step, when individuals enter the jail, a jail EHR record will be created (or an existing record will be opened for those with prior DCJ incarceration). Our automated algorithm will match the jail EHR to the Parkland EHR and generate an individual HIV risk score. For people with predicted HIV risk above a prespecified threshold that maximizes sensitivity without causing alert fatigue among providers, an automated prompt will appear in the jail EHR for providers to discuss PrEP and order HIV/STI testing. As illustrated in Figure 2, providers will also be prompted to order HIV/STI tests for any patients who report risk factors at intake or during a clinical assessment (eg, transgender identity and requests to be housed with MSM) or who request testing directly. Prompts will persist until orders are completed as a “nudge,” a behavioral economic intervention to maximize ordering [83], and results are entered into the EHR.

In the “engage” step, positive HIV tests will prompt referrals to the jail HIV clinic for rapid initiation of antiretroviral therapy according to the current practice, and STIs will be treated based on CDC guidelines [84]. Persons with negative HIV tests will meet one-on-one with a provider or PrEP navigator and receive counseling informed by our PrEP decision-support tool. The navigator we hire will be experienced in working with CL-involved people. Counseling will be person-centered and culturally tailored, with positive sexual health framing.

In the “navigate” step, for patients interested in PrEP, the navigator will review a list of PrEP clinic locations and assist with selecting a provider. Once an individual is released from the DCJ, the navigator will facilitate PrEP linkage by contacting that individual (by phone or SMS text messaging) and providing personalized care navigation. A hotline will be available for released individuals to call for assistance with PrEP referrals. The navigator will continue to follow referred patients for 3 months after any PrEP initiations, recording these contacts and clinical outcomes in REDCap, a secure online data capture system [85].

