### Potential Limitations and Alternative Approaches

In the process of refining the implementation strategy in our second aim, EHR models may be hampered by limited or missing data. We will minimize the missingness of EHR data by combining jail and Parkland data and extending this dataset over a 10-year timespan. We will explore the use of the missingness of EHR variables (which may be a proxy for not being engaged in primary care) as indicators to understand the effect on model performance. If model performance is suboptimal, we will rely primarily on patient-reported data to identify HIV risk. For EHR alerts, we will proactively address potential alert fatigue [95] by employing rigorous user-centered design principles [96]. We will also train providers on how to respond to alerts about HIV risk, as providers may be unaccustomed to these.

Delays in the generation of electronic HIV risk scores could result in the identification of individuals likely to benefit from PrEP after their release from jail. If this occurs, we expect to identify many of these individuals using patient-reported data. However, the model we have developed will generate scores on day 3 of each person’s incarceration, which will mitigate delays. We will also generate future EHR prompts for HIV/STI testing and PrEP if the patient returns to jail, and the navigator will contact the patient to encourage HIV testing and PrEP evaluations with community providers. Though patients may decline visits to discuss PrEP, we will maximize patient interest by training staff to present PrEP in a positive, discreet, and patient-centered manner and will offer our decision-support tool for patients to review independently. Since barriers, such as medical mistrust, transportation, and anticipated stigma, may limit patients’ access to PrEP, we will hire and train a navigator who is able to build rapport with diverse populations, use principles of trauma-informed care [97-99], and teach at many education levels. Additionally, we will access existing resources, such as care coordination, offered by community partners.

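### The risk model called ready to deploy was developed only on people HIV-tested in jail, so its pooled performance does not describe the entrants whom only the model would flag

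*Protocol article*

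**What the plan says.** **What was built.** The Results section of the protocol article reports a model that "has been developed using records from 33,458 individuals who have undergone HIV testing in jail". It is based on jail records and adds: "This model has been optimized using machine learning, has been internally validated, and is ready to be deployed". Linkage is still to come: "Future exercises will include integration with health system EHR data from Parkland Hospital and comparisons to parsimonious models".

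**What was planned.** Under Aim 2, the sections on datasets and on validation describe matched jail and Parkland records. The outcome is to include new HIV diagnosis codes as well as confirmed positive tests. Models are to be compared by the C-statistic and the Hosmer-Lemeshow test.

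**Where it is used.** Steps for Strategy Implementation says of people entering the jail: "Our automated algorithm will match the jail EHR to the Parkland EHR and generate an individual HIV risk score". Potential Limitations says that "the model we have developed will generate scores on day 3 of each person" is held. A provider prompt follows for "predicted HIV risk above a prespecified threshold that maximizes sensitivity without causing alert fatigue among providers". No value for the threshold, and no population on which it was derived, is given.

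**The other ways to be flagged.** The validation section adds further criteria alongside the model: "This will include anyone who identifies as transgender, requests MSM housing, has had a recent STI, or opts-in for HIV/STI testing". It then plans to compare the model with these criteria, giving as its example how many people each approach identifies that the other misses.

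**Who gets tested.** Study Setting describes testing as opt-in at intake and opt-out for those having blood drawn. It gives the yearly volume as follows: "Of over 12,000 HIV/STI tests performed each year at the DCJ", for a yearly population of 51,000.

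**The concern.** People tested in jail either asked for a test or were having blood drawn for some other reason. They are a selected group, and the alert is meant to reach beyond them by prompting tests that would not otherwise happen.

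The selection also overlaps with the comparison. Opting in to testing is both a route into the development data and a separate reason to be flagged. An opt-in tester who turned out to have HIV counts towards the model's sensitivity, yet would have been flagged without it. A good overall C-statistic can therefore say little about the people for whom the model is the only flag.

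Two decisions depend on this. The threshold trades sensitivity against alert burden, and both depend on the population scored. The added-value comparison is meant to show what the model contributes beyond the other criteria, but a count of extra people flagged does not show that those people are at higher risk.

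**Working it through.** **1. The plan's own figures.** The article gives no performance figure for the model, so there is none to reproduce. The one stated result that leans on it is the power of over 80% (Sustainment section). This compares 3 diagnoses in 250 tests a month with 9 in 500, over 24 months each, and attributes the rise to the model.

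- Events and tests: 3 × 24 = 72 in 6,000 before; 9 × 24 = 216 in 12,000 after.
- Log rate ratio: ln(0.018/0.012) = 0.405. SE = √(1/72 + 1/216) = 0.136.
- Power = Φ(0.405/0.136 − 1.96) = 84.6%, treating months as independent. The stated figure reproduces on that basis. How the assumed correlation of 0.2 enters is a separate question.
- If the first 250 tests keep their 1.2% yield, the added 250 must yield (9 − 3)/250 = 2.4%, twice the current yield.
- If the added tests yield 2.0%, 1.8% or 1.5% instead, the same formula gives power of 55%, 36% or 13%.

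This does not show the power to be wrong. It shows that the figure depends on how well the strategy, with the model at its centre, finds cases among people not tested now.

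**2. Share of entrants tested.** Inputs are from Study Setting.

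- With one HIV test per person: 12,000/51,000 = 23.5% tested, 76.5% not.
- On the power paragraph's volume: 250 × 12 = 3,000 tests a year, and 3,000/51,000 = 5.9% tested, about 94% not. The article does not reconcile the two volumes.
- Repeat or STI-only tests would raise the untested share. A volume above 12,000, or counting tests from earlier stays, would lower it.

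**3. What pooled sensitivity contains.** Let p be the share of diagnosed cases in the tested data already flagged by opting in, self-report or recent STI. Let S_a be the model's sensitivity in those cases and S_m its sensitivity in the rest. Then

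S = p·S_a + (1 − p)·S_m.

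The article gives none of these quantities. S_m equals S only if S_a = S_m (or p = 0), so a value of S alone does not determine S_m, in either direction.

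**4. Illustration of a fixed threshold (assumed, not from the documents).** Suppose scores in cases are normal and the threshold gives 80% sensitivity in tested people. If untested cases score s standard deviations lower, sensitivity in them is Φ(0.842 − s).

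| s | Sensitivity |
|---|---|
| 0 | 80% |
| 0.25 | 72% |
| 0.5 | 63% |
| 0.75 | 54% |
| 1.0 | 44% |

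The first row is as compatible with the article as the others. The table shows only that the question is worth checking.

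**The case against.** The case on the other side is substantial, and much of it stands.

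- **Threshold.** A reader might infer that it was set on tested people. The article does not say so, and a condensed article may leave its derivation to the full protocol.
- **Added-value count.** A reader might infer that people missed by patient-reported data can be counted only among blood-draw testers. The planned example counts people flagged, which needs a score and intake data but no HIV result, so untested people can be included. What remains is that such a count carries no information on risk.
- **Value of the alert.** It is not worthless for people who opt in. As written, the model prompt covers both testing and a PrEP discussion, while the prompt for self-reported risk or a test request covers only the tests.
- **Who is scored.** A reader might take every entrant to be scored. Scores come on day 3, so people released earlier have none, and 51,000 is not the size of the scored population.
- **Interim status.** Parkland integration is planned, refinement runs over 24 months, and patient-reported data are the fallback if the model performs poorly. Yield among newly tested flagged people can be observed in use. Sensitivity cannot, and the fallback may not be triggered if performance is judged only in tested people.
- **Blood-draw testers as a proxy.** They are themselves tested and selected by needing care, so they stand in only partly for the untested.

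None of this removes the central mismatch. Potential Limitations discusses missing record data but not selection into testing.

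**Conclusion.** The point holds in a limited form. The model declared deployable rests on jail records of tested people. Its intended use is not limited to them, and the Aim 2 plan and the implementation steps describe matched data. These sections need to be reconciled. Roughly three quarters of a year's entrants are untested that year, on the assumption of one HIV test per person and the rounded Study Setting volumes.

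Overall performance in tested people cannot stand for performance among those only the model would flag, because opting in is both a source of the data and a separate flag. This follows from the text without any assumption about the size or direction of a difference.

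The stronger conclusion a reader might draw is that the model fails in untested people, or that the planned comparison cannot show its worth. The documents support neither. Failure to transfer is an inference that they neither show nor exclude, and the sensitivity table above is an assumed range.

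**What to change.** 1. In the validation data, alongside the overall C-statistic and Hosmer-Lemeshow test, report sensitivity, positive predictive value and alert volume with 95% CIs among tested people who did not opt in and met no self-report or STI criterion.
2. Measure added value as new HIV diagnoses among people flagged by the model alone, not only as the number flagged.
3. Consider both alongside overall sensitivity when fixing the alert threshold.
4. Once Parkland data are linked, repeat the check in people not tested in jail who have Parkland tests or diagnosis codes.
5. Until then, state that performance applies to people tested in jail and that the blood-draw subgroup is a partial proxy for the rest.
6. Reconcile the Results section (jail records only) with the Aim 2 validation plan and the implementation steps (matched records).

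Items 1 to 3 are a re-analysis of data already held, provided the jail record shows whether each test was opt-in or opt-out; the article does not say that it does. The cost is fewer events, wider intervals and probably a less favourable stated sensitivity.

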## Discussion

### Expected Results

We anticipate that the implementation of the multicomponent strategy will promote robust linkage to PrEP care for many individuals at risk for HIV, which currently does not occur at the DCJ. Moreover, we expect to identify a higher number of new HIV infections and STIs than in the 2 years prior to implementation. Our final product will be a well-integrated sustainable multicomponent PrEP implementation strategy that starts upon jail entry and ends with linkage to community-based HIV prevention, which can address major HIV-related inequities for CL-involved populations.

### Potential Limitations and Alternative Approaches

In the process of refining the implementation strategy in our second aim, EHR models may be hampered by limited or missing data. We will minimize the missingness of EHR data by combining jail and Parkland data and extending this dataset over a 10-year timespan. We will explore the use of the missingness of EHR variables (which may be a proxy for not being engaged in primary care) as indicators to understand the effect on model performance. If model performance is suboptimal, we will rely primarily on patient-reported data to identify HIV risk. For EHR alerts, we will proactively address potential alert fatigue [95] by employing rigorous user-centered design principles [96]. We will also train providers on how to respond to alerts about HIV risk, as providers may be unaccustomed to these.

Delays in the generation of electronic HIV risk scores could result in the identification of individuals likely to benefit from PrEP after their release from jail. If this occurs, we expect to identify many of these individuals using patient-reported data. However, the model we have developed will generate scores on day 3 of each person’s incarceration, which will mitigate delays. We will also generate future EHR prompts for HIV/STI testing and PrEP if the patient returns to jail, and the navigator will contact the patient to encourage HIV testing and PrEP evaluations with community providers. Though patients may decline visits to discuss PrEP, we will maximize patient interest by training staff to present PrEP in a positive, discreet, and patient-centered manner and will offer our decision-support tool for patients to review independently. Since barriers, such as medical mistrust, transportation, and anticipated stigma, may limit patients’ access to PrEP, we will hire and train a navigator who is able to build rapport with diverse populations, use principles of trauma-informed care [97-99], and teach at many education levels. Additionally, we will access existing resources, such as care coordination, offered by community partners.

### Study Impact

Despite these possible limitations, this project will generate a valuable approach to prevent HIV in the disproportionately burdened population of CL-involved individuals in the Southern United States. As these individuals often have fragmented health care and may not be reached with approaches targeting primary care or STI clinics [100], our multicomponent implementation strategy has the potential to efficiently reach many persons likely to benefit from PrEP in a nontraditional but well-defined setting with rapid turnover to the larger community. Future projects will focus on adapting this strategy for dissemination to other urban jails, including those represented by our dissemination consultants, in HIV hotspots nationally to maximize its impact on the HIV epidemic for underserved minority communities.

## Abbreviations

CDC: Centers for Disease Control and Prevention
CL: criminal legal
DCJ: Dallas County Jail
EHE: Ending the HIV Epidemic
EHR: electronic health record
EPIS: exploration, preparation, implementation, sustainment
HARC: HIV/AIDS Re-Entry Coalition
HIPAA: Health Insurance Portability and Accountability Act
IRB: Institutional Review Board
MSM: men who have sex with men
PCCI: Parkland Center for Clinical Innovation
PrEP: pre-exposure prophylaxis
STI: sexually transmitted infection
